#### Inclusion criteria for clinicians

2.2.3

less than 5 years of clinical experience in influenza diagnosis or participation in national-level influenza research projects;Willingness to complete protocol-mandated tasks, including dual-round diagnosis (baseline vs. model-assisted) and post-study interviews;Currently practicing in a tertiary general hospital in Jiangsu Province.

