#### Phase IV: randomized controlled trial

2.3.4

This phase is a pragmatic randomised controlled design to assess the effectiveness of AI-assisted diagnosis in the real world. Clinicians will be assigned in a 1:1 ratio to either the control group (using standard clinical assessment protocols) or the AI model-assisted group. Allocation will be by block group randomisation, stratified by hospital level (urban vs. rural) and clinician experience level (resident, attending, chief) to ensure balanced representation in key subgroups.

The control group will rely exclusively on routine diagnostic workflows, while the model-assisted group will integrate AI outputs into their decision-making process and retain full authority to accept or reject recommendations. The primary outcome is the between-group AUC difference, with a ΔAUC greater than 0.15 defined as clinically significant, which is consistent with the U.S. Food and Drug Administration’s (FDA) benchmarks for diagnostic tools based on artificial intelligence or machine learning (AI/ML). The design simulates real-world clinical practice and quantifies the added value of AI in improving diagnostic accuracy while preserving clinician autonomy.

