#### Primary outcome

2.4.1

As the ultimate goal of this clinical trial is to create highly accurate AI models. Therefore the primary outcome metric was set as the area under the curve (AUC) (25). The AUC quantifies the discriminatory ability of the AI model so that it can distinguish patients who may develop severe influenza from those who will not. Since calculating the AUC requires the use of sensitivity, specificity, true positive rate, true negative rate, false positive rate, and false negative rate, more details describing these results can be found in our separate studies (16, 20).

To account for differences in diagnostic assessments after multiple clinicians read the cases, we planned to use the Dorfman-Berbaum-Metz (DBM) method. The DBM adjusts for differences in diagnostic assessments by clinicians so that AUC difference values between the two groups can be estimated (22). ROC curves were calculated using the pROC (version 1.18.0) software package (28). The AUC values as well as their 95% confidence intervals will then be calculated using MRMCaov (version 0.2.1) (27). For differences between the experimental and control groups, we expected to use the Mann-Whitney U test (29). Clinically significant improvement was defined as an AUC difference between the experimental and control groups greater than 0.15. The null hypothesis here is that the AUC difference is less than 0.7, and the AI model has no discriminatory power. Our method of using AUC to set thresholds not only follows statistical patterns, but is also highly compliant with the criteria for the development of AI-driven diagnostic tools.

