#### Randomization and allocation

2.6.1

A computer-generated randomization sequence will be created using the blockrand package in R, stratified by hospital tier (urban vs. rural) and clinician experience level (resident, attending, or chief physician). This approach ensures balanced allocation across subgroups, minimizing confounding effects from institutional resources or practitioner expertise. Participants will be assigned to either the control group (standard clinical diagnosis) or the model-assisted group (AI-supported diagnosis) at a 1:1 allocation ratio. The randomization sequence will be concealed in sequentially numbered, opaque envelopes managed by an independent statistician to prevent selection bias, ensuring equitable distribution of participants and maintaining trial integrity.

To ensure unbiased group assignment, an independent statistician uninvolved in recruitment or data analysis will prepare opaque, sequentially numbered envelopes containing group allocations (control or model-assisted). These sealed envelopes will be securely stored and only opened sequentially by a dedicated study coordinator after clinicians complete baseline assessments. This procedure rigorously prevents selection bias by concealing allocation details until the point of intervention assignment, thereby safeguarding the randomization integrity and ensuring equitable distribution of participants across study groups.

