#### Primary outcome analysis

2.8.1

The AUC will serve as the primary metric to evaluate the diagnostic accuracy of the AI model. To account for variability inherent in multi-reader, multi-case study designs, the DBM method will be employed, which adjusts for differences in clinician interpretations and case complexity. Analyses will be conducted using the MRMCaov (v0.2.1) and pROC (v1.18.0) packages in R, generating AUC values with 95% confidence intervals (CIs) derived from non-parametric bootstrapping (1,000 iterations). A clinically significant improvement is predefined as a ΔAUC more than 0.15 between the model-assisted and control groups, with the null hypothesis assuming no discriminative capacity (AUC less than 0.70, equivalent to random guessing). This approach ensures robust statistical inference while addressing real-world diagnostic variability across clinicians and settings. Hyperparameter optimization was conducted via Bayesian optimization with 5-fold cross-validation, prioritizing AUC on the validation set.

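### Phase IV stratifies the randomisation of clinicians by hospital tier and experience, but the stated primary AUC comparison uses neither factor, at a small cost in precision

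*Protocol article*

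**What the plan says.** **Allocation.** Section 2.3.4 (Phase IV) makes the clinician the unit of randomisation: "Clinicians will be assigned in a 1:1 ratio to either the control group" or the model-assisted group. Section 2.6.1 repeats that the sequence is "stratified by hospital tier (urban vs. rural) and clinician experience level (resident, attending, or chief physician". That is 2 × 3 = 6 strata. The same section has the envelopes "only opened sequentially by a dedicated study coordinator after clinicians complete baseline assessments".

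**Primary analysis.** Section 2.8.1 states that "the DBM method will be employed, which adjusts for differences in clinician interpretations and case complexity", with AUCs from MRMCaov and pROC and intervals from 1,000 bootstrap iterations. Section 2.4.1 adds: "For differences between the experimental and control groups, we expected to use the Mann-Whitney U test". Neither section mentions a stratum term, stratified resampling or a baseline term.

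**Where the factors return.** Tier and experience appear again only as subgroup variables (2.4.3 and 2.8.3). The regression in 2.8.3 belongs to the subgroup analyses, and the confounders it gives as examples are season, viral load and treatment delay.

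**The concern.** Stratified allocation makes the two arms alike on tier and experience. If those factors predict diagnostic accuracy, the AUC difference varies less from one randomisation to another than it would under simple randomisation. An analysis that omits the factors does not see this. It counts variation between strata as error and reports too large a standard error.

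The reader component of DBM does not repair this. DBM treats readers as a source of variance. In a crossed design such as Phase III, where every clinician reads under both conditions, differences between clinicians cancel from the comparison. In Phase IV clinicians are nested within arm, so a chief physician's advantage over a resident stays in the reader error. The Mann-Whitney test in its standard form takes no strata or covariates.

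At stake are the width of the interval for the AUC difference and some power. Validity is not threatened.

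**Working it through.** **1. The plan's own sample size (2.5.1).** Inputs: AUC 0.85 and 0.70, Z values 1.96 and 1.645. The variance term is V = 0.85 × 0.15 + 0.70 × 0.30 = 0.3375.

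n = (1.96 + 1.645)² × 0.3375 / 0.15² = 12.996 × 15 = 194.9, or 195 per group.

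Section 2.5.2 prints 145, which is therefore not reproduced. By the same formula, power is Φ(0.15/√(0.3375/145) − 1.96) = 87.5% at 145 and 92.6% at 174 per group. That mismatch is a separate matter. What matters here is that V is a per-patient quantity and holds no between-clinician component.

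**2. Inputs the document does not give.** These are the between-clinician SD of AUC, the share of it that the strata explain, the severe proportion, and whether the arms share cases. All are assumptions below.

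**3. Strata only, simulated.** Assumptions: binormal ratings, three experience levels, 20% severe, 174 patients per group, 1,500 trials per scenario. Tier was not included.

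| AUC gap between adjacent levels | SE unadjusted | SE adjusted | Ratio | Rejection rate, unadjusted → adjusted |
|---|---|---|---|---|
| 0.10 | 0.0598 | 0.0592 | 1.010 | 74.3% → 75.3% |
| 0.15 | 0.0591 | 0.0577 | 1.024 | 76.9% → 78.8% |

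Each rejection rate has a Monte Carlo error of about √(0.75 × 0.25/1500) = 1.1 points, so the SE ratio is the steadier measure. Putting these SEs into Φ(0.15/SE − 1.96) gives 70.8% → 71.7% and 71.8% → 73.9%, gains of 0.9 and 2.0 points.

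**4. Cross-check by variance components.** Take 109 clinicians per arm (2.5.2) and separate patients in each arm. The Hanley-McNeil case variance of the difference at 174 per group and 20% severe is 0.0683² = 0.00466. With equal thirds by experience, a gap g adds a clinician variance of g² × 2/3, and a contribution of 2 × (g² × 2/3)/109 to the difference.

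- g = 0.10: 0.000122, which is 0.000122/(0.00466 + 0.000122) = 2.6% of the total. The SE is too large by 1/√(1 − 0.026) − 1 = 1.3%.
- g = 0.15: 0.000275, which is 5.6% of the total. The SE is too large by 2.9%.

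This is close to the simulated 1.0% and 2.4%.

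**5. Wider ranges.** Let the clinician SD run from 0.03 to 0.10, the share explained from 10% to 50%, and the severe proportion from 10% to 50%. With separate patients, adjustment lowers the total variance by 0 to 3.5%. If instead all 348 cases are read in both arms, with a between-arm case correlation of 0.5 to 0.95, much of the case variance cancels and the reduction is 0.1 to 31%.

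**6. Direction of the error.** A clinician-level simulation (216 clinicians, six strata, 3,000 runs, no case variance) tested at a nominal 5% without the strata. The type I error was 3.6% when strata explain 10% of clinician variance and 2.2% when they explain 30%. With adjustment it was 4.7% and 5.8%. The unadjusted test is therefore conservative. These figures overstate the effect in the trial itself, where case variance is added.

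**The case against.** **Left to an analysis plan.** The strongest objection is that a condensed article may leave model covariates and bootstrap strata to a full analysis plan, and that 2.8.1 nowhere calls the analysis unadjusted. This has weight for DBM and the bootstrap. It has less for 2.4.1, which names a between-group test that takes no covariates, although it is worded as an expectation and stands beside DBM.

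**Small size and no bias.** The loss is small and the estimate unbiased. Both points stand, and they set the weight of the finding.

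**A stronger reading about baseline.** Because the envelopes are "opened sequentially by a dedicated study coordinator after clinicians complete baseline assessments", a reader might infer that the plan also discards a baseline accuracy score. The document does not show that such a score exists. The phrase "dual-round diagnosis (baseline vs. model-assisted" in 2.2.3 fits the two rounds of Phase III, and no Phase IV text says what the pre-allocation assessment records.

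**A stronger reading about power.** A reader might also multiply the variance in the 2.5.1 formula by (1 − ρ²). At ρ = 0.5 this would lift power at 145 per group from 87.5% to 94.8%. That does not hold: a clinician-level covariate cannot reduce case-sampling variance, which is all the formula contains. Even the 3.5% upper figure for separate patients moves that power only from 87.5% to 88.6%.

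**Shared cases.** The larger reductions need both arms to read the same cases. Section 2.5.2 counts patients per group and 2.6.3 ties patients' care to their group, which points to separate patients. The text does not settle it.

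**Conclusion.** The mismatch is in the text: tier and experience define the Phase IV randomisation and are absent from the stated primary comparison. The consequence is a modest loss of precision and a conservative test.

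With separate patients, 20% severe cases and AUC gaps of 0.10 to 0.15 between adjacent experience levels, the standard error is about 1 to 2.5% too large and about 1 to 2 power points are lost. Smaller differences between levels would make it negligible; shared cases could make it larger. The document supplies none of these inputs, so the range is illustrative.

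The document does not support reading this as a bias in the AUC difference, or as the reason the sample size falls short of its own formula.

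**What to change.** In 2.4.1 and 2.8.1, for Phase IV:

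- Estimate the AUC difference from a model, for example on the jackknife pseudovalues DBM already uses, with fixed effects for arm, hospital tier (2 levels) and experience (3 levels). Enter tier and experience as main effects rather than six cells, so that sparse strata do no harm.
- Cluster by clinician, or resample clinicians within arm and stratum, for the standard error and interval.
- Replace the Mann-Whitney test as the primary comparison, and report the unadjusted difference as a sensitivity analysis.
- State whether the arms read the same cases. With separate patients there are about 348/218 = 1.6 per clinician, and the pseudovalues would have to be formed within arm rather than within clinician.
- Add the clinician's unassisted baseline accuracy as a covariate only if the assessment before allocation does record one.

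The cost is 3 degrees of freedom (1 for tier, 2 for experience), or 4 with the baseline covariate, plus wording and a few lines of code. Tier and experience are known at allocation, so no new data are needed. The choice should be fixed before outcome data are seen, so that the adjusted and unadjusted results are not compared first.

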#### Secondary outcomes analysis

2.8.2

Secondary endpoints include diagnostic sensitivity and specificity, calculated using the Clopper-Pearson exact method for binomial proportions to determine the model’s and clinicians’ ability to correctly identify true positive and true negative cases, respectively. Differences between clinician and model performance will be assessed via the Mann–Whitney U test, a non-parametric method suitable for skewed distributions. Positive and negative predictive values (PPV/NPV) will be adjusted for influenza prevalence using Bayes’ theorem and reported with 95% confidence intervals to reflect their clinical utility in real-world settings. The misdiagnosis rate, defined as the sum of false positives and false negatives per 100 diagnoses, will be analyzed using an independent samples t-test (if normally distributed) or Wilcoxon rank-sum test (for non-normal data), quantifying the model’s impact on reducing diagnostic errors. These metrics collectively evaluate the model’s precision, reliability, and practical value in augmenting clinical decision-making.

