#### Phase III: multi-reader, multi-case validation

2.3.3

Phase 3 used a two-round diagnostic design for evaluating the impact of AI model assistance on the effectiveness of clinician decision-making. The AI models used in Phase 3 were calibrated in the Phase 2 validation phase. Recruited clinicians are split into two rounds subsequently evaluating cases independently then filling in the diagnosis.

The first round of tasks that clinicians receive is the baseline diagnostic assessment. In the baseline diagnostic assessment, clinicians are required to evaluate cases using a standard influenza diagnostic protocol and subsequently complete the diagnostic results.

The second round of tasks allows clinicians to access the risk scores and key influencing factor scores generated by the AI model to fill in the diagnosis during the evaluation of the case.

All clinicians were required to undergo two rounds of tasks. This was done with reference to a previous study (22). The use of machine-assisted diagnosis by clinicians can increase their productivity (23). To minimise bias, cases are randomly reordered between rounds of assessment and a 4-week washout period is set between assessments to reduce recall effects. Diagnostic accuracy (measured as AUC) and clinician confidence (scored on a 5-point Likert scale) will be compared between rounds of assessment to quantify the impact of the model on decision consistency and clinician certainty. This multi-reader, multi-case framework ensures robust assessment of AI-human collaboration while addressing variations in real-world clinical work.

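### Clopper-Pearson intervals are named for clinicians' sensitivity and specificity with no allowance for shared cases or repeated readers; if multi-reader readings are pooled, the nominal 95% intervals are too narrow

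*Protocol article*

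**What the plan says.** Section 2.8.2 (Secondary outcomes analysis) of the protocol article states that sensitivity and specificity are "calculated using the Clopper-Pearson exact method for binomial proportions", and applies this to the model and to the clinicians alike. One method is named for both, without restriction by phase and without a unit of analysis. The 95% level in that section is attached to the predictive values ("reported with 95% confidence intervals"); I assume the same level for sensitivity and specificity.

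Section 2.3.3 describes Phase III as a multi-reader, multi-case study. "All clinicians were required to undergo two rounds of tasks", and "cases are randomly reordered between rounds of assessment and a 4-week washout period is set between assessments to reduce recall effects". The cases are reordered, not replaced, so each clinician reads the same material twice. The comparisons that section names are AUC and clinician confidence. Section 2.3.2 (Phase II) is where sensitivity and specificity are named as metrics for clinicians with and without the model.

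For the AUC, section 2.8.1 recognises the dependence: "the DBM method will be employed, which adjusts for differences in clinician interpretations and case complexity". It then says that the AUC confidence intervals are "derived from non-parametric bootstrapping (1,000 iterations", without giving the resampling unit. Section 2.4.1 takes the same intervals from the MRMCaov package.

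**The concern.** Clopper-Pearson inverts a single binomial distribution with independent trials. With one call per patient, as for the model alone, that is appropriate. Clinician readings in a crossed design are different: a hard severe case tends to be missed by several readers at once, and a reader with a high threshold misses many cases. If all readings go into one numerator and one denominator, the interval is computed as if readers times cases were that many separate patients.

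The plan would then treat the same kind of reading as dependent for its primary outcome and independent for its secondary one. Section 2.4.2 presents these secondary endpoints as showing whether the tool reduces missed severe cases, so the stated precision of clinician sensitivity matters to how the results are read.

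**Working it through.** **Inputs.** From the article: the interval method (2.8.2); the crossed, two-round layout (2.3.3); 218 clinicians and 348 patients overall (2.5.2, 2.5.3). Not given, so assumed: readers per case set (5, 10, 20), severe cases (35, 70), true sensitivity 0.75, and probit-scale SDs of 0.1-0.3 for readers and 0.2-1.0 for cases. The article states no interval width or coverage of its own to reproduce.

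**Step 1: design effect.** For R readers crossed with D severe cases, with intraclass correlations ρc (same case) and ρr (same reader), the variance of the pooled proportion is inflated by approximately

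DEFF = 1 + (R − 1)ρc + (D − 1)ρr,

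and a nominal 95% interval misses with probability about 2Φ(−1.96/√DEFF).

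The assumed SDs translate to the binary scale by ρ = [Φ₂(z, z; r) − p²] / [p(1 − p)], where p = 0.75, z = Φ⁻¹(p), and r is the variance component divided by the total (1 + reader variance + case variance):

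- reader SD 0.1, case SD 0.2: ρc = 0.021, ρr = 0.005
- reader SD 0.3, case SD 0.5: ρc = 0.105, ρr = 0.037
- reader SD 0.3, case SD 1.0: ρc = 0.293, ρr = 0.023

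For 10 readers and 35 severe cases:

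- small effects: 1 + 9 × 0.0207 + 34 × 0.0051 = 1.36, miss about 9%
- middle: 1 + 9 × 0.105 + 34 × 0.0367 = 3.19, miss about 27%
- large case effect: 1 + 9 × 0.2927 + 34 × 0.0234 = 4.43, miss about 35%

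**Step 2: simulation.** Simulating crossed binary calls and applying Clopper-Pearson to the pooled count gives:

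| Readers × severe cases | Small effects (0.1, 0.2) | Larger effects (0.3, 0.5-1.0) |
|---|---|---|
| 5 × 35 | about 7% | up to about 24% |
| 10 × 35 | about 9% | 26-33% |
| 20 × 70 | about 11% | 39-50% |

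Separate runs differ by a few points, and the design-effect formula agrees to the same degree. With no reader or case effect, the same code misses 4-5%, so the excess comes from the dependence.

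**Step 3: width.** At 10 × 35 the pooled Clopper-Pearson interval is about 0.093 wide. The width needed for 95% coverage (3.92 × the true SD) is about 0.105 with small effects and 0.16-0.19 with the larger ones.

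**Step 4: where the problem does not arise.** An interval for one clinician on that clinician's own readings missed that clinician's true sensitivity about 3% of the time. In a nested Phase IV layout, with 348/218 ≈ 1.6 patients per clinician, non-coverage stays below 5%. For the model alone there is one call per patient.

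**The case against.** **Pooling is not stated.** Section 2.8.2 gives no unit of analysis, and per-reader Clopper-Pearson intervals are ordinary and valid. This stands, and makes the point conditional. But the section speaks of clinicians collectively, and it names a method that is wrong for the collective estimate.

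**Phase III does not list sensitivity or specificity.** Also true: section 2.3.3 lists AUC and confidence. The secondary analysis is not limited by phase, however, and Phase II does name both metrics for clinicians. Whether Phase II clinicians share cases is not spelled out. Sharing in Phase III is implied by the design label and the use of DBM rather than stated outright.

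**The size rests on assumptions.** It does. With small effects and few readers the excess is only a few points. A reader might be tempted to put all 218 clinicians on one case set, which would push non-coverage above 50% in most scenarios. The article does not support that: 218 is 109 per group, and nowhere are all of them said to read a common set.

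**Non-coverage is not a false-positive rate.** A reader might infer that chance differences between assisted and unassisted reading will look established at these rates. That does not follow. The plan uses Clopper-Pearson for single proportions and assigns the clinician-model comparison to a Mann-Whitney test, and the two rounds share readers and cases. With no true difference and effects fully shared between rounds, a naive two-proportion test rejected in only 1-4% of simulated runs; with half the effect variance shared, in 13-72%. The effect on differences therefore turns on a between-round correlation that the article does not give.

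**The AUC bootstrap.** One might read section 2.8.1 as resampling individual readings, which would discard the dependence. It does not say so; resampling whole readers and cases is also non-parametric bootstrapping. Only a wording mismatch with section 2.4.1 remains.

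**Conclusion.** The point holds in conditional form. The plan names an independent-trials interval for clinicians' sensitivity and specificity, although its multi-reader design correlates the readings and it adopts a method for that correlation only for the AUC. If readings are pooled across shared cases, the direction of the error is certain: the interval is too narrow. Its size is not fixed by the article. It runs from a few points above the nominal 5% with small reader and case effects to a third of intervals at 10 × 35 and about half at 20 × 70 with larger ones. These figures concern a single pooled proportion, not the test of a difference. The matter affects secondary endpoints and can be settled before analysis.

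**What to change.** - State the unit of analysis for clinician sensitivity and specificity in section 2.8.2, by phase.
- Keep Clopper-Pearson for the model alone and for any intervals reported clinician by clinician.
- For reader-averaged clinician sensitivity and specificity, and for their assisted-minus-unassisted difference, take confidence intervals from the random-reader, random-case analysis already planned for the AUC, applied to the binary calls. A bootstrap that resamples whole clinicians and whole cases is an alternative.
- Reconcile sections 2.4.1 and 2.8.1 so that the multi-reader AUC interval comes from the DBM analysis, or from a bootstrap whose units are stated to be whole readers and whole cases.

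This changes analysis wording and code only; design and recruitment are untouched. The price is wider intervals for clinician accuracy.

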#### Inclusion criteria for patients

2.2.1

Laboratory-confirmed influenza virus infection via nucleic acid testing [reverse transcription polymerase chain reaction (RT-PCR)] or rapid antigen testing, adhering to China’s *Diagnosis and Treatment Protocol for Influenza*;All age groups;Written consent obtained from patients: (a) patients with full civil capacity (more than 18 years); (b) Legal guardians for minors (less than 18 years), incapacitated adults, or patients with cognitive impairment.

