#### Phase V: prospective validation study

2.3.5

As Dai et al. illustrate the point, using prospective cohort data validation provides a better view of the model’s performance in the real world (24). This final phase evaluates the model’s real-world clinical utility during the 2025 influenza season. The AI model will be deployed in real time to analyze EHRs of newly admitted influenza patients across all 87 hospitals. Clinicians will receive model-generated predictions (such as risk scores, key contributing factors) within 2 h of case entry via a secure, institution-specific dashboard.

Data collection will capture:

Clinician actions: Initial diagnosis (pre-model assessment), final diagnosis (post-model review), and time-to-decision (minutes from case entry to diagnosis).Model performance: Concordance between model predictions and ground truth (severe influenza confirmed by an independent adjudication panel).

This prospective design validates the model’s operational feasibility, diagnostic timeliness, and accuracy in dynamic clinical environments, providing critical evidence for scalability and regulatory approval.

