#### Secondary outcomes

2.4.2

Secondary endpoints include diagnostic sensitivity and specificity, defined as the proportion of true severe influenza cases correctly identified by the model or clinicians, which reflects the tool’s capacity to minimize missed diagnoses in high-risk populations (30).

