#### Intervention groups

2.6.3

In the control group, clinicians (without any AI assistance) will diagnose influenza cases using standard clinical protocols, integrating symptoms, laboratory results, and imaging findings. Patients in this group will receive routine care based solely on clinician assessments.

In contrast, the model-assisted group will utilize a secure digital dashboard providing real-time AI predictions, including a risk score (0–100%) for severe influenza progression and highlighted contributing factors (such as prolonged fever duration, abnormal lymphocyte counts).

While the model offers data-driven insights, its outputs are non-prescriptive; clinicians retain full authority to accept, modify, or reject recommendations, ensuring clinical judgment remains central to decision-making. This design balances technological support with practitioner autonomy, reflecting real-world diagnostic workflows.

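### The Bayes adjustment of PPV and NPV names influenza prevalence, but every patient has influenza and the condition being diagnosed is severe influenza

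*Protocol article*

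**What the plan says.** The protocol article, section 2.8.2 (Secondary outcomes analysis), sets the rule: "Positive and negative predictive values (PPV/NPV) will be adjusted for influenza prevalence using Bayes", completed by the word for the theorem. The results are to carry 95% confidence intervals and to speak to real-world clinical utility. No prevalence value or source is given.

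Other sections fix the population and the target condition:

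- **Population.** Section 2.2.1 requires "Laboratory-confirmed influenza virus infection via nucleic acid testing" or a rapid antigen test. In Phase V (2.3.5) the model runs on "newly admitted influenza patients across all 87 hospitals".
- **Target of the AUC.** Section 2.4.1 describes the model's discriminatory ability as being such that "it can distinguish patients who may develop severe influenza from those who will not".
- **Target of sensitivity and specificity.** Section 2.4.2 has them "defined as the proportion of true severe influenza cases correctly identified by the model or clinicians".
- **Reference standard.** Section 2.3.5 names "severe influenza confirmed by an independent adjudication panel".
- **Model output.** Section 2.6.3 describes a 0–100% risk score "for severe influenza progression and highlighted contributing factors".

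No section redefines influenza prevalence to mean the prevalence of severe influenza.

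**The concern.** Bayes' theorem turns sensitivity and specificity into predictive values through the pre-test probability of the condition that those two measures describe. The sections above make that condition severe influenza. The adjustment rule instead takes the prevalence of influenza, which is an entry criterion and not the diagnosis at issue.

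Predictive values tell a clinician how far to trust a high-risk or low-risk flag, and of the planned accuracy measures they depend most on prevalence. An analyst who follows 2.8.2 to the letter would look up or compute an influenza prevalence. The resulting PPV and NPV would not describe the patients on whom the tool is used.

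**Working it through.** **Inputs.** The article states no PPV, NPV, prevalence, sensitivity or specificity for this calculation, so there is no figure to reproduce. Every numerical input below is an assumption except the 100%, which follows from the inclusion criterion in 2.2.1.

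**Formulas**, with Se = sensitivity, Sp = specificity, p = prevalence:

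- PPV = Se·p / [Se·p + (1 − Sp)(1 − p)]
- NPV = Sp(1 − p) / [Sp(1 − p) + (1 − Se)p]

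**Step 1: influenza prevalence among enrolled patients, p = 1.** The term (1 − p) is zero, so PPV = Se/Se = 1 and NPV = 0/(1 − Se) = 0. This holds for any Se and Sp strictly between 0 and 1. The two measures become constants that carry no information from the data.

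**Step 2: other values of p, assumed Se = Sp = 0.80.**

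| Assumed p | PPV | NPV |
|---|---|---|
| 5% | 0.04 / (0.04 + 0.19) = 0.174 | 0.76 / (0.76 + 0.01) = 0.987 |
| 10% | 0.08 / (0.08 + 0.18) = 0.308 | 0.72 / (0.72 + 0.02) = 0.973 |
| 20% | 0.16 / (0.16 + 0.16) = 0.500 | 0.64 / (0.64 + 0.04) = 0.941 |
| 30% | 0.24 / (0.24 + 0.14) = 0.632 | 0.56 / (0.56 + 0.06) = 0.903 |

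**Step 3: direction of the error.** It depends on which prevalence is larger.

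- Influenza figure inserted 30%, true severe proportion 10%: PPV is reported as 0.632 against a correct 0.308, overstated by a factor of 2.1.
- Influenza figure inserted 5%, true severe proportion 20%: PPV is reported as 0.174 against a correct 0.500, understated.

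**Step 4: sensitivity to the assumed accuracy.** With Se = Sp = 0.85, PPV runs from 0.230 at p = 5% to 0.708 at p = 30%, and NPV from 0.991 to 0.930. With Se = Sp = 0.90, PPV runs from 0.321 to 0.794 over the same range. In each case the choice of prior moves PPV much more than NPV.

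**The case against.** The strongest reply is that a word was dropped. Every operational section names severe influenza as the target, and nobody would deliberately plan a PPV fixed at 1 and an NPV fixed at 0 and then attach confidence intervals to them. That is plausible. But the article separates influenza from severe influenza in its eligibility, outcome and adjudication sections, and the rule in 2.8.2 names the former. Nor is this a detail left to an analysis plan: the article states the rule, and the rule names the wrong quantity.

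A second reply is that little hangs on it. PPV and NPV appear only in 2.8.2, are not listed among the outcomes in 2.4.2, and have no hypothesis, threshold or role in the sample size. This stands, and it limits the weight of the point.

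A reader might also infer that the rule must inflate PPV, perhaps several-fold. The article does not support that. A ratio near six arises only by setting the degenerate 100% reading against the lowest assumed severe proportion in the table (1.00/0.174 = 5.7). The severe proportion among admitted patients is not given and could be high: the Introduction cites an influenza mortality of about 20%, and death is among the endpoints verified in 2.4.5. That figure may not suit this cohort, but it shows that a severe proportion above the inserted influenza figure cannot be ruled out. PPV would then be understated.

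**Conclusion.** The point holds as an error in the stated rule. Section 2.8.2 uses a prior for a condition that all patients already have, while sensitivity, specificity and the reference standard concern severe influenza. In the enrolled population the literal rule gives PPV 1 and NPV 0, and this needs no assumption beyond the inclusion criterion and Se and Sp strictly between 0 and 1. With an external influenza prevalence, the predictive values would be right only by coincidence.

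The size and sign of the error under that second reading cannot be fixed from the article. The illustrated PPV range of 0.17 to 0.63 rests on assumed sensitivity and specificity of 0.80 and assumed prevalences of 5% to 30%. The consequence is confined to secondary metrics, since the AUC does not use the prevalence.

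**What to change.** In section 2.8.2, replace *influenza prevalence* with *the prevalence of adjudicated severe influenza among laboratory-confirmed influenza patients in the intended-use setting*, and name the source. The Phase V cohort is the natural source if its admissions are unselected. The article does not say that they are consecutive, so the sponsor should confirm this.

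Where the Phase V case mix is unselected, report the observed PPV and NPV directly. Keep the Bayes adjustment for phases whose cases were selected.

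Two cautions apply when Phase V supplies the prevalence. Section 2.4.5 describes panel review of cases classified as severe, so severe cases classified otherwise could go uncounted. Clinicians also see the model output in Phase V, which could alter care and hence the observed rate of progression. Both should be acknowledged beside the estimate.

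The cost is a phrase and a source statement in 2.8.2. Severe progression (yes/no) is already a planned data item in Table 2, so no new variable is needed. The Phase V data are still to be collected according to 2.7.2.
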